## Abstract

**Background:**

Fatigue is one of the most common and debilitating symptoms of multiple sclerosis (MS). The majority of approaches for managing MS fatigue typically require participation in a structured, time-limited program with a fixed sequence of topics and activities. MS INFoRm (Multiple Sclerosis: An *In*teractive *F*atigue Management *R*esource) is a self-directed MS fatigue management resource incorporating principles of self-management and adult learning. Positive results from a feasibility pilot study of a USB-delivered version of MS INFoRm led to the current trial and adaptation of MS INFoRm to a website format. The specific aims of the proposed study are to (a) to determine the effectiveness and efficacy of 3-month use of MS INFoRm on fatigue impact (primary outcome) among persons with MS, (b) to determine whether 3-month use of MS INFoRm results in improvement in secondary outcomes of self- efficacy for managing MS fatigue, self-reported cognitive function, participation and autonomy, and depression, and (c) to determine whether any improvements in primary and secondary outcomes are maintained among the MS INFoRm users after 6-months.

**Methods/Design:**

Parallel group, two arm, double-blinded superiority trial with a 1:1 allocation. Two hundred persons with MS will be randomly assigned to either an intervention (MS INFoRm) or usual care control group in which they will be given 3-month access to either the MS INFoRm website (intervention group) or a control webpage containing widely available resources on MS fatigue (control group). Baseline, immediate post-intervention (3-months), and follow-up (6-months post intervention) evaluations will take place on primary (Modified Fatigue Impact Scale) and secondary (Multiple Sclerosis Self-Efficacy Scale, Perceived Deficits Questionnaire, Center for Epidemiologic Studies Depression Scale, and Impact on Participation and Autonomy Questionnaire) measures. Hypothesis testing will involve independent samples t-tests and mixed effects ANOVAs.

**Discussion:**

People with MS may benefit from easily accessible and self-directed fatigue management resources based on self-management and adult learning principles. The proposed study will provide crucial evidence about the potential of MS INFoRm as a self-management tool that can be made widely available to persons with MS as a means to effectively reduce the daily impact of MS fatigue.

**Trial registration:**

ClinicalTrials.gov: NCT03362541. Posting date December 5, 2017.

## Background

People with MS experience a wide range of symptoms, including fatigue [1]. At least two-thirds of people with MS report clinically significant fatigue [2] that negatively impacts employment [3], quality of life [4] and ability to engage in a full range of daily activities [5, 6]. People who have MS describe fatigue as frustrating, overwhelming, and disabling [7]. Presence of MS fatigue has been linked to increased risk of falls [8], comorbidities [9], and use of health care services among people with the disease [10].

MS fatigue has both primary and secondary components, that is, it is both intrinsic to the disease and a function of factors such as deconditioning, poor sleep and nutrition, and stress [6, 11]. As a consequence, management of this symptom can be challenging. To date, treatments have included medications and the rehabilitative approaches of energy management training, cognitive behavioral therapy, and exercise [12, 13]. Across these options, medications are the least effective [14]. Trials of rehabilitative options have uncovered effect sizes in the moderate range [14], with energy management training and cognitive behavioral therapy demonstrating effectiveness for a broader range of people with MS (e.g., levels of disability, age, etc.) [14].

The major limitation of all existing and effective approaches for managing MS fatigue is that they require the individual with MS to participate in a structured, time-limited program that has a fixed sequence of topics and activities. In some cases, participation requires travel to a treatment site [15, 16]. Although internet options exist [13, 17], regular and scheduled participation are still required. Adult learning theory suggests that self-directed approaches to learning and behaviour change may be more effective than structured approaches because they allow adults to maintain their own self-concept; build on life experiences, social roles and motivations; and facilitate immediate application of knowledge in daily life [18]. In addition, literature on self-management suggests that supporting individuals to take control of their chronic conditions leads to better health outcomes [19, 20]. Together, the limitations of existing interventions, knowledge of adult learning theory, and principles of self-management led our team to ask whether a self-directed MS fatigue management intervention would enable people with MS to reduce the impact of this symptom on their daily life. In response, we developed MS INFoRm (Multiple Sclerosis: An *In*teractive *F*atigue Management *R*esource) which incorporates approaches previously identified as being effective for managing MS fatigue [14].

The initial version of MS INFoRm (initially developed in 2012) was an interactive Microsoft PowerPoint Presentation with embedded hyperlinks to worksheets and pdf files, with the entire resource provided via USB key. The contents of MS INFoRM include ways to monitor fatigue, information on how to effectively communicate with others about MS fatigue and when and where to go for help. It also explains several common secondary sources of fatigue (depression, sleep disorders, medications, lack of physical activity, mental exertion) and offers evidence-based energy management strategies that can be used in the context of daily life. We have published pilot findings from the original USB version of MS INFoRm in which 35 individuals with MS who reported mild to moderate fatigue were provided with MS INFoRm to use at home for 3 months, on their own volition [21]. Participants reported actively using MS INFoRm over this period. Three-month use of MS INFoRm was associated with significant reductions in fatigue impact, increased knowledge of MS fatigue, and greater confidence in managing MS fatigue. Our pilot study also included qualitative analysis of semi-structured interview with participants, which revealed that 3-month use of MS INFoRm was associated with shifts in knowledge, expectations, and behaviours with respect to fatigue management. These shifts led to multiple positive outcomes, including increased levels of self-confidence and improved quality of life [22].

Given our promising pilot results, the need for easily accessible interventions that can be used independently to support self-management skill development, we will now conduct a further larger randomized controlled trial of a website version of MS INFoRm. The trial will randomly assign an anticipated 200 participants to one of two conditions: (1) 3-month access to the MS INFoRm intervention website and (2) 3-month access to a “usual care” control website that provides widely available fatigue management resources. The control website was designed to represent the usual care and resources that persons with MS are directed to by their physicians or other health care providers. The specific aims and hypotheses are described below.

### Specific aim 1

Our first aim is to determine the effectiveness and efficacy of 3-month use of MS INFoRm on fatigue impact among persons with MS. Our primary outcome will be measured using the Modified Fatigue Impact Scale (MFIS) [23]. We hypothesize that the MS INFoRm group will show significant reductions in fatigue impact compared to the usual care control group.

### Specific aim 2

Our second aim is to determine whether 3-month use of MS INFoRm results in improvement in secondary outcomes of self- efficacy for managing MS fatigue, self-reported cognitive function, depression, and participation and autonomy. The measures we will use to evaluate these outcomes are the Multiple Sclerosis Self-Efficacy Scale (MSSES) [24], the Perceived Deficits Questionnaire (PDQ) [25], Center for Epidemiologic Studies Depression Scale (CES-D) [26], and Impact on Participation and Autonomy Questionnaire (IPA) [27] respectively. We hypothesize that the MS INFoRm group will show significant improvements in self-efficacy for managing MS fatigue, self-reported cognitive function, participation and autonomy, and significant reductions in depression, compared to the usual care control group.

### Specific aim 3

Our third and final aim is to determine whether any improvements in primary and secondary outcomes are maintained among the MS INFoRm users after 6-months. We hypothesize that the beneficial effects of MS INFoRm will be maintained at 6-month follow-up.

## Methods

### Study design, recruitment and location

This study will utilize a parallel group, two arm, superiority trial with a 1:1 allocation. Both participants and outcome assessors are blinded to group allocation. Participants will be recruited from across Canada via internet advertisements (MS Society of Canada Research Portal and MS group social media pages based in Canada). Participants will also be recruited from 3 MS clinics in Edmonton, Calgary, and Kingston located in academic hospitals (University of Alberta, University of Calgary, Queen’s University) by having MS clinic staff hand out study flyers. A last method of recruitment will be study flyers placed within the local Kingston, Ontario community. Our expected recruitment is 50 participants per site (Edmonton, Calgary, Kingston) and another 50 participants from internet advertisements. All recruitment methods will direct potential participants to contact the research team located at Queen’s University in Kingston, Ontario. All screening of participants, provision of website access and troubleshooting, and baseline and outcome assessment will be conducted by the research team at Queen’s University. Recruitment started in January 2018 and is anticipated to be completed by May 2019. If recruitment strategies are failing to generate necessary numbers of participants, backup sites for additional recruitment have been identified.

### Eligibility criteria

In order to be eligible for participation, an individual must: (1) have MS, (2) be between 18 and 65 years of age, (3) have access to a computer or other electronic device with internet access on which to review MS INFoRm, (4) have an average score between 2.0 and 5.4 across the 9 items of the Fatigue Severity Scale (FSS) [28], and (5) live in Canada. This last inclusion criteria is to minimize any confounding that may be introduced by differences in usual care across health care systems. Individuals will be excluded if they have any one of the following: (1) any major comorbid conditions that might influence fatigue management (lupus, rheumatoid arthritis, chronic obstructive lung disease, chronic fatigue syndrome), (2) report difficulty reading and comprehending English, (3) report upper extremity or visual impairments that cannot be accommodated adequately to enable computer access, (4) report depression based on a Patient Health Questionnaire-2 score [29] of 3 or more, (5) demonstrate evidence of cognitive impairment based on a Short Blessed Test [30] score or 12 or more.

### Group allocation

Group allocation will be based on a random permutated block design, using computerized random number generation. This design was selected because it ensures a 1:1 allocation ratio between the intervention group and the control group and because it will effectively reduce any risk of a systematic bias that may confound the treatment effect (i.e., people from the same MS clinic enrolling sequentially). The block size, which is fixed, will not be disclosed, to ensure concealment. One hundred people will be allocated to the MS INFoRm group and 100 to the usual care control group.

All eligible participants will be provided with a study identification number and password to access the MS INFoRm website. Using the block randomization process described above, each study ID has been assigned to one of the two groups by two of the study investigators. A password-protected file, and the MS INFoRm administrator website, which includes the group allocation for each Study ID, is only be accessible by two of the study investigators. Upon login, participants in the MS INFoRm intervention group will be directed to the intervention website whereas participants in the usual care control group will be directed to the usual care website. Participants will be provided with access to the website for 3-months from time of baseline assessment. Participants will access the website at their own volition, and not be directed on how often to use it as the nature of the intervention is self-directed, in order to replicate real-world use.

### MS INFoRm intervention website

A description of the sections, content, and features of the MS INFoRm intervention website is provided in Table 1.

**Table 1 Tab1:** MS INFoRm intervention website content and features

Section	Primary Content and Features
1. Initial login page	- Presents introductory video providing user with orientation to website and overview of MS fatigue
2. Basics of fatigue	- Provides definition of fatigue - Provides facts about MS fatigue including prevalence, association with other disease-related factors, and how MS fatigue is different than regular fatigue - Provides description of primary and secondary fatigue - Includes section on tracking fatigue, including description of the benefits of tracking fatigue, how to track fatigue using a printable form, or on the “Rate your Fatigue” section (described below in section 3) of the website - Provides a link to the introductory video (enables users to review initial login page information)
3. Rate your fatigue	- Allows users to rate fatigue level at each visit (limits to one entry per day) from 0 (lowest fatigue) to 10 (highest fatigue) - Presents all ratings in a line graph that shows date and time, and rating
4. Track your goals	- After initial login page, users are prompted to set at least one fatigue management goal - Users are prompted to enter the following for each goal: (a) What do you want to do? (b) When do you want to start doing it? (c) How often do you want to do it? (d) How will you know that you have achieved this goal? (e) How confident are you that you can achieve this goal? - Users can update the answers to question (e) and are asked to rate the goal completion progress at each subsequent login - Users can have 3 goals active at a time, any goals that become achieved are put in a “Goals History” page - Users are prompted to select up to three fatigue management strategies to use to help them accomplish each goal. Strategies are described and can be selected from Sections 5 and 6 (described below) of the website
5. Influencing factors	Each of the following influencing factors, or contributors to secondary fatigue are provided on separate webpages
i. Poor sleep	- Describes the prevalence of poor sleep in persons with MS, causes of poor sleep (e.g. pain, stress, depression), definition and signs and symptoms of poor sleep, and common sleep disorders in persons with MS (insomnia, restless legs syndrome, and sleep apnea) - Describes when to talk to a healthcare professional regarding poor sleep - Describes 11 sleep hygiene strategies that can be used to improve sleep quality, and includes a link to a pdf sleep diary that can be used to track sleep and use of sleep hygiene strategies
ii. Medication side effects	- Describes how fatigue can be a side effect of medications - Describes use of medications for MS fatigue - Describes strategies for managing medication side effects and includes a link to a pdf medication side effects diary
iii. Deconditioning	- Defines physical activity, exercising, and deconditioning - Describes how getting enough physical activity can improve fatigue - Guides users about how to start an exercise program - Provides strategies for being more physically active, one of which includes working towards meeting the “Canadian Physical Activity Guidelines for People with MS” (description of these guidelines provided)
iv. Cognitive fatigue	- Provides a definition of cognitive fatigue, and contributing factors - Provides a description and examples of cognitive rehabilitation strategies that can help improve cognitive fatigue
v. Depression	- Provides a definition, and describes signs and symptoms, and prevalence of depression in MS - Describes when to get help for depression and includes a link to pdf version of the Patient Health Questionnaire-2. Users are encouraged to make an appointment with their health care provider if their score adds up to 3 or more - Describes how depression is treated in MS (pharmacological and non-pharmacological approaches) - Describes strategies for managing depression (e.g. participating in therapy, talking to healthcare provider about possibility of taking antidepressant medication)
6. General fatigue	- Describes principles of energy management and provides examples and strategies for how to bank and budget energy. A link to a pdf “Rest Scheduling Worksheet” is provided to help users with banking energy - Describes strategies for talking to other people about MS fatigue and asking for help, including five audio examples. Section also includes a link to a pdf handout which can be filled out and given to friends, family, or caregivers as a tool to teach others about MS fatigue and ask for help - Provides examples and strategies for modifying activities in order to use energy more wisely
7. Next steps	- Provides a summary of main points from website and things to remember - Provides quotes from people with MS who are working to manage their fatigue - Provides links to additional resources about MS fatigue (e.g. from MS Society of Canada, National MS Society, MS International Federation, etc.)

### Usual care website

The usual care website includes links to widely available brochures/ pdfs published by the MS Society of Canada entitled “MS Fatigue” [31] and “Living Well With MS: Managing Fatigue” [32]. These pdfs were chosen as they are resources to which clinicians, including those on the research team, often direct their MS patients. A brief description of the contents of each brochure/ pdf is provided on the website prior to presenting the link. The usual care website was designed to visually resemble the intervention website in order to facilitate blinding. We acknowledge, however, that some participants might be able to recognize that they have been allocated to the usual care control group if they have been previously exposed to the usual care resources.

### Secondary outcomes

Four secondary outcomes will be measured, including self-efficacy, perceived cognitive function, depression, and participation and autonomy. Self-efficacy will be measured using the Multiple Sclerosis Self-Efficacy Scale (MSSES) [24], which consists of 14 items. Respondents rate the degree to which they believe they can overcome challenges using a 6-point Likert scale, ranging from “strongly disagree” to “strongly agree”. A high score indicates high self-efficacy. Validity, reliability and sensitivity to change of the MSSES has been established [24].

The Perceived Deficits Questionnaire (PDQ) will be used to measure perceived cognitive function [25]. The full-length PDQ consists of 20 items assessing the cognitive functions most commonly affected in MS: attention, retrospective memory, prospective memory, and planning and organization. Respondents rate problems in these areas according to their frequency from 0 (never) to 4 (almost always) in the past 4 weeks, with higher scores indicating worse perceived cognitive functioning. The PDQ was developed specifically for persons with MS [25], and is associated with objective cognitive performance [34].

The Center for Epidemiologic Studies Depression Scale (CES-D) will be used to measure depression [26]. The CES-D has been found to be a valid and reliable scale to assess depressive symptomatology in MS [35]. This measure consists of 20 items describing depression-related symptoms that are rated according to frequency in the last week from 0 (rarely or none of the time) to 3 (all of the time). A cut-off score of 16 or higher is suggestive of clinically significant depressive symptoms [26].

The Impact on Participation and Autonomy Questionnaire (IPA) will be used to measure participation and autonomy [27, 36]. The IPA provides a measure of limitations in participation and autonomy and is a commonly used measure for evaluating rehabilitation outcomes in individuals with chronic disease, including MS [37, 38]. The tool includes 39 questions across 5 domains: autonomy indoors, autonomy outdoors, family role, social life and relationships, and work and education. Participants rate each item on scale from 0 (very good) to 4 (very poor). The scoring captures how likely respondents feel they will be able to participate in a described activity or how their disability impacts their ability to participate. Higher scores indicate greater restrictions. The IPA has been shown to have strong psychometric properties, including reliability, validity and responsiveness to intervention [36, 37, 39].

### Sample size

We seek to recruit a total of 200 individuals. The total number of individuals to be recruited is based on calculations of sample size and power for a balanced independent-groups mixed effect model with three time points for our primary outcome (i.e., fatigue impact at baseline, 3 months, 6-months post use). The effect sizes, variances and covariance estimates were obtained from our pilot results [21]. Calculations take into account potential attrition over time, which could be as high as 34% based on our pilot study. This high attrition rate, however, was likely due to limited persistence of research staff for follow-up assessments, which we will attempt to remediate in the proposed project.

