Hypothesis 1 states that the MS INFoRm group will show significant reductions in fatigue impact compared to the usual care control group. In order to test hypothesis 1, changes between baseline and 3-month scores on the MFIS will be compared between the MS INFoRm group and the usual care control group using an independent t-test. If the testing for group equivalence indicates that there are baseline differences between the groups at baseline, an analysis of variance with covariates will be used to test hypothesis 1. A *p* < 0.05 will be used as the significance value. In order to test efficacy, or whether MS INFoRm works when delivered as intended, data from only those individuals who have complete baseline and 3-month data and have accessed all of the website content at least once will be used in the analysis. In order to test effectiveness, participants who have missing 3-month scores will be assigned a change score of zero.

Hypothesis 2 states that the MS INFoRm group will show significant improvements in self-efficacy for managing MS fatigue, self-reported cognitive function, participation and autonomy, and significant reductions in depression, compared to the usual care control group. The analysis will use the same approach as hypothesis 1, using zero-value change scores for individuals lost to follow-up. A Bonferroni adjustment will be applied for multiple testing, and therefore the significance value will be set at *p* < 0.0125 (0.05/4 tests).

Hypothesis 3 states that the beneficial effects of MS INFoRm will be maintained at 6-month follow-up. To address this hypothesis, a mixed-effect ANOVA will be used with an unstructured variance-covariance structure, a random intercept and terms for both a linear and quadratic trend. A quadratic trend would be characterized by a sharp improvement immediately post-intervention (3-months), followed by a gradual stabilization of improvement. The five measures (MFIS, MSSES, PDQ, CES-D, and IPA) will be modelled simultaneously and individually. When modelled simultaneously, a significance value of *p* < 0.05 will be used. When modelled individually, a Bonferroni adjustment will be applied for multiple testing, and therefore the significance value will be set at *p* < 0.01 (0.05/5 tests).

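### The target of 200 was sized for a three-visit mixed model with effects from a pilot that, as described, had no comparator, so it does not give the power of the primary 3-month t-test

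*Protocol article*

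**What the plan says.** - **Target.** Under Sample size: "We seek to recruit a total of 200 individuals". Group allocation splits this equally: "One hundred people will be allocated to the MS INFoRm group and 100 to the usual care control group".
- **Basis.** The target rests on "calculations of sample size and power for a balanced independent-groups mixed effect model with three time points for our primary outcome", the three points being baseline, 3 months and 6 months after use ends.
- **Inputs.** "The effect sizes, variances and covariance estimates were obtained from our pilot results". The same section says attrition was allowed for and might reach 34%, as in the pilot. It expects better follow-up this time.
- **Pilot.** The Background describes it as follows: "35 individuals with MS who reported mild to moderate fatigue were provided with MS INFoRm to use at home for 3 months". No comparator is mentioned.
- **Primary test.** Under Statistical analysis, Hypothesis 1, "changes between baseline and 3-month scores on the MFIS will be compared between the MS INFoRm group and the usual care control group" by an independent t-test at p < 0.05. Covariates enter only if a baseline comparison finds differences. In the effectiveness analysis, a missing 3-month score counts as no change.
- **Where the mixed model is used.** Only under Hypothesis 3 (maintenance), for five measures including the MFIS.

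**The concern.** Two stated methods do not meet.

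1. **Model.** The sizing model uses three visits and their covariances. The primary test uses two visits and makes no use of the third (month 9 in Table 2).
2. **Effect.** A two-group model needs an assumed difference between groups. A pilot in which everyone received the intervention supplies a before-after change, which mixes any effect of MS INFoRm with regression to the mean and non-specific improvement. The trial's control arm gets a similar-looking website linking to two fatigue brochures, under attempted blinding, so some improvement among controls is plausible.

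The Dissemination plan makes wider release depend on the hypotheses being supported. A null primary result would then be judged against a power calculation made for another analysis and possibly for another contrast.

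**Working it through.** **Inputs from the article:** 100 per arm; attrition up to 34%, so 200 × 0.66 = 132 completers, 66 per arm; alpha 0.05. **Assumed:** two-sided testing, equal loss in both arms, and d = between-arm difference in mean change divided by the SD of change. Power is by the normal approximation, Φ(d√(n/2) − 1.960). The noncentral t changes results by less than one percentage point.

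**1. Can 200 be reproduced?** No. The article gives no effect size, SD, correlation or power, which an article may leave to the full protocol. Inverting it for the t-test at 80% power, d = 2.802 × √(2/n):
- n = 100 per arm: d = 0.396
- n = 66 per arm: d = 0.488

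So 200 would suit a t-test for d near 0.49 with 34% loss (66/0.66 = 100 per arm). The article does not say that this was the basis.

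**2. Size of the model mismatch.** Assume compound symmetry with correlation ρ, a sustained effect of 0.4 score SD and 66 per arm. The SD of change is √(2(1 − ρ)).

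| ρ | 3-month change t-test | 2-df group-by-time test | Mean of both follow-ups minus baseline |
|---|---|---|---|
| 0.5 | 63% | 66% | 76% |
| 0.7 | 84% | 88% | 93% |

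Across ρ of 0.5 to 0.8, a mixed-model calculation exceeds the t-test's power by about 2 to 12 points, depending on which contrast was used.

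**3. Effect of the zero rule.** With missing share m and true mean change μ (SD 1), an arm has mean (1 − m)μ and variance (1 − m)(1 + μ²) − ((1 − m)μ)². For m = 0.34, d = 0.5 and unchanged controls:
- Difference in means: 0.66 × 0.5 = 0.33
- Variances: 0.66 × 1.25 − 0.33² = 0.716 (intervention) and 0.66 (control)
- Standardised difference: 0.33/√0.688 = 0.398
- Power with 100 per arm: Φ(0.398 × √50 − 1.960) = 80%
- Power with 66 completers per arm: Φ(0.5 × √33 − 1.960) = 82%

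The estimate shrinks by 34%, but the variance shrinks too. At d = 0.40 the same comparison is 62% against 63%. With zeros it falls to 58% and 54% only if controls improve by 0.4 and 0.6 SD.

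**4. Effect of taking a before-after change as the between-arm effect.** Illustration with a pilot change of 0.5 SD (not a figure from the article):

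| Control improvement (SD) | Remaining between-arm d | Power, 34% zeros | Power, 66 completers per arm |
|---|---|---|---|
| 0 | 0.5 | 80% | 82% |
| 0.1 | 0.4 | 61% | 63% |
| 0.2 | 0.3 | 39% | 41% |
| 0.3 | 0.2 | 20% | 21% |

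This is the largest of the three effects.

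**5. What baseline adjustment would give at the same N.** The residual SD is √(1 − ρ²). For 0.4 score SD and 66 per arm:
- ρ = 0.5: 0.4/0.866 = 0.462, power Φ(0.462 × √33 − 1.960) = 76%, against 63% for the change t-test
- ρ = 0.7: 0.4/0.714 = 0.560, power 90%, against 84%

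The noncentral t gives 75% and 89%.

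**The case against.** **The calculation matches a planned analysis of the primary outcome.** This stands. Hypothesis 3 models the MFIS at the same three visits. A reader might infer that the calculation describes no part of this trial. It fails to describe the primary Hypothesis 1 test only.

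**Attrition was already allowed for.** This largely stands. A reader might infer that zero-filling invalidates the allowance. Step 3 shows that dividing by 1 − 0.34 covers nearly all of the power cost unless controls improve substantially. The 34% is also a stated upper limit, with reminders and four contact attempts planned to reduce it. The zero rule mainly affects the size of the estimate. It is right only if people who are lost truly did not change.

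**The pilot effect may have been discounted.** This is possible. That the pilot had no control arm is an inference from its description, and the article does not say that the raw change was entered as the between-arm effect. But the article names the pilot as the source of the effect sizes and mentions no allowance for change in controls.

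**No harm to the sample size is shown.** This stands. A reader might infer that 200 is too few. Without the effect size, SD and correlations, the article supports neither that reading nor its opposite.

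**Conclusion.** The concern holds in limited form. The stated basis for 200 belongs to the Hypothesis 3 type of model and draws its effects from a pilot with no described comparator. It therefore neither gives the power of the primary 3-month t-test nor rests on a stated difference from the usual care website. A fuller document could add the missing numbers, but the difference between the two stated methods would remain.

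On size, the choice of model is worth about 2 to 12 points of power under the assumed correlations. Unallowed improvement among controls could cost far more: from 80% to 61% for each-arm loss of 34% and only 0.1 SD of control improvement, if a 0.5 SD pilot change had been used. Zero-filling shrinks the estimated difference by about the missing share, up to 34%, with little further loss of power. These figures rest on two-sided testing, equal loss in both arms, compound symmetry and illustrative effect sizes. The point should be corrected, but it is no reason to enlarge the trial.

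**What to change.** Keep 200 participants.

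1. Make the primary analysis the group difference in MFIS at 3 months from the repeated-measures model. Adjust for baseline MFIS in every case, not only when a baseline test is significant. Use all observed data without zero-filling.
2. Keep the zero-change rule as a sensitivity analysis. The new primary analysis relies on missingness being explained by the observed data, and the zero rule tests a pessimistic alternative.
3. Restate the detectable between-arm 3-month MFIS difference for that analysis at 200 enrolled and at 132 completers, labelling the latter as the stated worst case. As a guide at 80% power with baseline adjustment alone, 66 per arm detects 0.488 × √(1 − ρ²), which is 0.42 score SD at ρ = 0.5 and 0.35 at ρ = 0.7. With 100 per arm the figures are 0.396 × √(1 − ρ²), or 0.34 and 0.28.
4. Take only the SD and correlations from the pilot. Justify the between-arm difference separately, with an explicit allowance for change in controls.

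**Cost:** a protocol amendment to the primary test, one recalculation and a rewritten Sample size paragraph. The stated detectable effect may look less favourable than the one now implied. No extra participants or visits are needed.
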